## Abstract

**Background:**

Atrial fibrillation (AF) is a common arrhythmia that requires anticoagulation therapy to prevent stroke. However, there is still a significant under-/over-treatment in stroke prevention for patients with AF. The adherence and the risk of bleeding associated with oral anticoagulation therapy (OACs) are major concerns. Shared decision-making (SDM) is an approach that involves patients and healthcare providers in making decisions about treatment options. This study aims to assess the effectiveness of a novel SDM tool for anticoagulation management in AF.

**Methods:**

The study will be a prospective, cluster randomized controlled trial involving 440 patients with AF in 8 community health service centers (clusters) in Shanghai, China. The SDM group will receive anticoagulation management through the novel SDM tool, while the control group will receive standard care. The follow-up period will be at least 2 years. The primary outcome will be any bleeding event, while secondary outcomes include the accordance of stroke prophylaxis for AF according to the current guidelines, time in therapeutic range (TTR), the occurrences of major bleeding and thrombosis events, and patient knowledge, adherence, and satisfaction.

**Discussion:**

This study will provide evidence of the effectiveness of shared decision-making in improving the appropriateness of OAC use in Chinese AF patients. The findings may inform the development of guidelines and policies for the management of AF and anticoagulation therapy in China and other countries.

**Trial registration:**

ChiCTR ChiCTR2200062123. Registered on 23 July 2022.

**Supplementary Information:**

The online version contains supplementary material available at 10.1186/s13063-023-07667-5.

## Background

Atrial fibrillation (AF) is a chronic cardiac arrhythmia that is prevalent worldwide, affecting 2 to 4% of the population [1]. In China alone, it affects more than 10 million patients [2]. It is crucial to note that AF substantially increases the risk of stroke by fivefold [3]. Several studies have established that oral anticoagulants (OAC), including warfarin or non-vitamin K antagonist oral anticoagulants (NOACs), are essential for preventing stroke in AF patients [4–7]. However, in clinical practice, suboptimal OAC usage is a common occurrence [8]. Over a third of AF patients who are eligible for OAC treatment receive antiplatelet therapy instead [9]. The Shanghai cross-sectional survey revealed that only 29.5% of AF patients received anticoagulation, and 40.1% were treated with antiplatelet agents for stroke prevention [10]. Additionally, more than a quarter of patients receiving OAC are underdosed or overdosed [11]. Approximately 90% of the study population in Taiwan received a lower dosage of NOACs in 2016 [12]. A Korean national study showed that 40–60% of patients were also provided with lower doses of NOACs [13]. Our epidemiological meta-analysis of 23 studies involving 162,474 AF patients found that the overall prevalence of off-label NOAC doses was 24%, with underdosing accounting for 20% and overdosing for 5% [14]. The inappropriate use of OACs can be attributed to various factors, including clinicians’ lack of understanding of the indications and recommended use of OACs and patients’ excessive concerns about the bleeding risk associated with OACs [15–17]. Patient adherence is also a significant factor affecting anticoagulation quality. After 1 year, medication adherence is at 70% among AF patients, dropping to 50% at 2 years and only 35% after 5 years [18]. In conclusion, inappropriate usage and non-adherence to OAC can result in poor outcomes and high costs for AF patients [18, 19].

Shared decision-making (SDM) is a crucial process that involves both medical professionals and patients in treatment decision-making, leading to improved rationality, reduced decision conflict, and increased patient satisfaction and adherence [1]. This approach is now recommended as a class I recommendation for patient management in clinical guidelines for AF [1]. Although several online tools have been developed to facilitate SDM in AF patients [20–23], most of them use outdated or nonspecific data and lack support for full-process follow-up, making it challenging to achieve optimal individualization of anticoagulation and sustainable management [23]. In response to these challenges, our team developed a SDM tool called I-Anticoagulation, which comprises two functional modules—an anticoagulation decision support system and a full-process patient management system—to enhance the decision-making and patient management of stroke prevention in AF [24]. In the I-Anticoagulation tool, risk estimation for stroke and bleeding is based on Asian patient data, and the corresponding NCB of each optimal anticoagulation strategy are calculated. Clinicians and patients can use this tool to gain a clear understanding of the risks of anticoagulation therapy and engage in a conversation to analyze the advantages and disadvantages of available recommendations and make a shared decision. During the follow-up period, the CHA2DS2-VASc score and the HAS-BLED score are updated with the changes in patient risk factors, and the NCB for each anticoagulant and corresponding recommendations also change dynamically. Accurate recognition of patient risk and precise recommendations for anticoagulation can improve the rationality of anticoagulation therapy, as well as patient adherence and satisfaction. In a pilot study, the use of I-Anticoagulation improved rationality, adherence, and satisfaction in both medical professionals and patients [24]. However, the pilot study had a limited sample size, and only patients using I-Anticoagulation were included in the analyses. Therefore, this study aims to evaluate the effectiveness of the SDM tool in improving the quality, patient adherence, and satisfaction of anticoagulation therapy in AF patients through a prospective, multicenter, cluster randomized controlled trial. In addition to these primary objectives, our research also contains exploratory objectives that aim to broaden our understanding of the SDM tool’s impacts:To assess the impact of the SDM tool on patient-clinician provider communication and explore if the tool enables a more effective and interactive dialog around anticoagulation management.To evaluate the cost-effectiveness of the SDM tool within the scope of community health service centers. This assessment will look at both direct and indirect medical costs related to anticoagulation management and will aim to discern if the SDM tool can bring about economic benefits by reducing overall cost.

## Methods

### Study design

This study will be a cluster randomized controlled trial conducted from October 2022 to April 2024 in eight community health service centers in Shanghai, China. The trial will compare the efficacy of using the shared decision-making (SDM) tool, I-Anticoagulation, versus the usual care in treating patients with AF. The clusters will be randomly assigned to either the SDM or control group, as depicted in Fig. 1. Consecutive patients with AF will be enrolled in the study, with those in the SDM group being treated using the I-Anticoagulation tool, while those in the control group receiving standard care. The study was registered on July 23, 2022, in the Chinese Clinical Trial Registry, with the registration number ChiCTR2200062123. This protocol was designed and described according to the standard protocol item—Recommendations for Interventional Trials–Artificial Intelligence (SPIRIT-AI) extension published in 2019 [25] (see Additional file 1).

**Fig. 1 Fig1:**
[figure not shown]
Flow chart of the study. AF, atrial fibrillation; ECG, electrocardiogram; SMD, shared decision-making; TTR, the percentage of time in the target INR range; AKT, Anticoagulation Knowledge Tool; MARS-5, Medication Adherence Reporting Scale; ACTS, Anti-Clot Treatment Scale

### Patient and public involvement

Neither the public nor the patients were engaged in the proposal of the research question, the design or implementation of the study, or patient recruitment. The results will be dispersed to the study participants via public reports and academic papers.

### Settings and participants

This study will enroll patients who are 18 years or older and have received a new diagnosis of paroxysmal, persistent, or permanent AF confirmed by electrocardiogram (ECG) or 24-h Holter monitors and are willing to participate in the study and sign the informed consent. Patients who meet any of the following criteria will be excluded: those who are pregnant, have experienced therapeutic or subtherapeutic bleeding complications in the last 6 months, have severe renal insufficiency (creatinine clearance rate, CrCl ≤ 20 ml/min), have severe hepatic insufficiency (Child–Pugh ≥ 10 points), have severe heart failure (cardiac function New York Heart Association, NYHA grade IV and above), have severe infection and respiratory failure, or are unable to comply with the study requirements. Patients can reserve the right to drop out due to any reason or without reason and at any time during the study. If any incident happens to the patients, such as death, disability, or dementia, they could withdraw from the study after applying by their legal representatives and evaluating by researchers. The full eligibility criteria are listed in Table 1.

**Table 1 Tab1:** Inclusion and exclusion criteria

**Inclusion criteria**
Aged ≥ 18 years
Diagnosed with new-onset, paroxysmal, persistent, or permanent AF confirmed with electrocardiogram (ECG) or 24 h Holter monitors
Patients or guardians agree to the study plan and sign the informed consent form
**Exclusion criteria**
Pregnant patients
Patients who experienced therapeutic or subtherapeutic bleeding complications in the past 6 months
Patients with severe renal insufficiency (CrCl ≤ 20 ml/min)
Patients with severe hepatic insufficiency (Child–Pugh ≥ 10)
Patients with severe heart failure (NYHA grade IV and above)
Patients with severe infection and respiratory failure

*AF* atrial fibrillation, *CrCl* creatinine clearance rate, *NYHA* New York Heart Association

### Recruitment

In order to ensure a sufficient number of participants, the recruitment methods will involve a combination of some approaches. Firstly, electronic medical records will be used to identify the potential participants who meet the inclusion criteria. Secondly, these potential patients will be reached out through mailings and phone calls. Additionally, we will establish a collaboration with physicians across various departments in community health centers involved in the research, to refer patients who meet the criteria to our study. To enhance recruitment, advertisements on online platforms and social media, such as WeChat Official accounts, will be used to raise awareness about the study and encourage participation.

Each center will aim to recruit approximately the same number of participants per month to ensure a balanced distribution of participants across the study duration. Based on this, the estimated recruitment per center per month will be approximately 3 participants (440 participants/18 months/8 centers).

After the screening, the participants who meet the eligibility criteria will be recruited. To ensure a comprehensive and efficient recruitment process, a trained doctor in the department of cardiology from each community health service center involved in the study will collaborate with a clinical pharmacist to facilitate and monitor the recruitment process. In addition, each center will have a dedicated research assistant who will serve as the project’s focal person throughout the study duration. The contact information of recruited participants will be collected and securely stored. The potential participants will be provided with detailed information about the study both in written and verbal formats. They will also be given consent forms, which will clearly state their rights to withdraw from the study at any point. Once the participants have been fully informed and have provided their consent, they will be enrolled in the study and assigned unique code numbers by the principal investigator (PI).

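### Enrolment is described as consecutive, but physician referral and online advertising are also used in an open cluster trial, so the sample is not consecutive and entrants can differ by arm

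*Protocol article*

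**What the plan says.** Study design (protocol article): "Consecutive patients with AF will be enrolled in the study".

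Recruitment lists four routes:
- Record search: "electronic medical records will be used to identify the potential participants who meet the inclusion criteria".
- Outreach: "these potential patients will be reached out through mailings and phone calls".
- Referral: physicians in various departments of the participating centres are asked "to refer patients who meet the criteria to our study".
- Advertising: "advertisements on online platforms and social media, such as WeChat Official accounts, will be used to raise awareness about the study and encourage participation".

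The same section adds a pace, "Each center will aim to recruit approximately the same number of participants per month", and estimates it at about 3. It says that those who meet the criteria at screening are recruited. A cardiology doctor at each centre, working with a clinical pharmacist, facilitates and monitors recruitment.

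Randomization and blinding: allocation is by centre, each centre's administrator learns that centre's result by telephone, and researchers, participants and analysts are all unblinded.

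Strengths and limitations: people who agree to take part may care more about their health and adhere better. The article presents this as a threat to generalizability.

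**The concern.** Consecutive enrolment means that every eligible patient is approached as he or she appears, so that neither staff nor patients choose who is considered. It is the only safeguard against such choice that the article states. Advertising and referral without a completeness rule set it aside.

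In an individually randomized trial with concealed allocation, this would mainly affect whom the results apply to. Here the centre is randomized and the trial is open. Once a centre's arm is known, the arm of every later patient there is known before consent. A physician at a tool centre may refer a different kind of patient from a physician at a usual-care centre, and a patient may volunteer because the tool is on offer. The arms could then differ in bleeding risk at entry, and that difference would appear in the primary comparison of any bleeding. The same applies to adherence, a secondary outcome, which is the trait the article says volunteers may have more of.

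A report that called the patients consecutive would also be inaccurate.

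**Working it through.** **The pace figure.** Inputs from Recruitment: 440 participants, 18 months, 8 centres.
- 440 / 18 / 8 = 3.06 per centre per month, which agrees with the stated approximate 3.
- 440 / 8 = 55 per centre in total.

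The figure reproduces. It is worded as an aim and an estimate, with no cap, quota or waiting list.

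**Each route against the claim of consecutive enrolment.**

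| Route | Compatible with consecutive enrolment? |
|---|---|
| Record search, then mail and telephone | Yes, if every eligible patient found is invited in a fixed order; the article states no such order |
| Referral by centre physicians | Only if every eligible patient is referred; no such rule is stated |
| Online and WeChat advertising | No; entrants select themselves |
| Monthly aim of about 3 | Yes, as an approximate pace |

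Advertising alone is enough to make the description wrong. Referral without a completeness rule adds to it.

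**Whether selection can differ by arm.** Three statements combine:
1. Centres are the unit of allocation (Study design).
2. The result goes to someone at each centre, and researchers and participants are unblinded (Randomization and blinding).
3. Recruitment is run locally over about 18 months (Recruitment), and the article names no recruiter who is masked to the centre's arm.

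From the moment a centre's staff know its arm, selection can depend on it. When that moment falls is not fully explicit: allocation is placed after AF confirmation, and only the administrator is named as being told.

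**Size.** If a share *h* of an arm is high risk, its bleeding rate is *h* × (high-risk rate) + (1 − *h*) × (lower-risk rate). The documents give only the overall 20% (Sample size). They give no risk groups and no expected difference in mix between arms, so the bias cannot be calculated.

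To show the mechanism only, assume that 30% of patients are high risk and 35% of those bleed.
- Lower-risk rate = (20 − 0.3 × 35) / 0.7 = 13.57%.
- Arm with 20% high risk: 0.2 × 35 + 0.8 × 13.57 = 17.86%, or 2.1 points below 20%.
- Arm with 10% high risk: 0.1 × 35 + 0.9 × 13.57 = 15.71%, or 4.3 points below 20%.

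The 30%, the 35% and the shifts are all assumptions with no source in the documents.

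**The case against.** The strongest reply is that most of the Recruitment section fits consecutive enrolment. A record search with mailings and calls is a way to find all eligible patients, referral within the centres can serve the same end, and the text says that those who meet the criteria will be recruited. This stands for the record search. It stands for referral only if referral is complete, which is not stated. It does not stand for advertising.

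A reader might infer something stronger: that the level monthly number forces centres to pass over eligible patients in busy months, so that the two rules cannot both be followed. The text does not support this. The number is an approximate aim with no cap, and the article gives a reason for it, an even spread over the study. It applies alike to all eight centres and both arms, so it creates no difference between them. Similar accrual also helps keep cluster sizes and calendar time comparable.

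A reader might also take the illustrative shifts, 2.1/15 = 14% to 4.3/15 = 29% of a 15-point effect, as the expected bias. The arithmetic is right, but the inputs are invented for illustration and nothing in the documents makes such a shift likely.

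Finally, a screening log or a sensitivity analysis may sit in the full protocol or the analysis plan, neither of which is shown. That is fair, and their absence from the article is not the point. The point is that two descriptions in the article conflict.

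**Conclusion.** The concern holds in a limited form. The article calls enrolment consecutive and then describes routes, advertising above all, that are not. Because centres are allocated openly and recruit locally, the mix of entrants can differ between arms. That is a matter of internal validity as well as of generalizability, and the article acknowledges only the latter.

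The conclusion rests on the text and on one assumption: that staff or patients at a centre know its arm while patients are still being recruited. This is likely in an unblinded trial with centre-level allocation, although the timing is not spelled out. Neither the direction nor the size of any bias can be derived from the documents, so no number should be attached to it. The monthly aim should be left as it is.

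**What to change.** 1. For the rest of enrolment, have each centre invite every eligible patient found by the record search in a fixed order, for example by date of the qualifying ECG or Holter recording.
2. Have the research assistant already assigned to each centre keep a log of eligible, invited, refused and enrolled patients, by centre and route of entry (record search, referral, advertisement or self-referral).
3. Repeat the primary analysis without advertisement and self-referred entrants. This analysis will be less precise than the main one, and agreement with it would not rule out selection through referral; the log helps to judge that.
4. If advertising or referral stays, replace the word consecutive in Study design with a description of the actual routes. In Strengths and limitations, say that volunteer selection may differ between arms.

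The cost is some added record keeping, one further analysis and a change of wording. Sample size and interventions are unaffected. Enrolment began in October 2022, so the invitation order cannot be applied to patients already entered, and their route of entry may not be recoverable. If it is not, the sensitivity analysis should report how many patients have an unknown route.

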### Randomization and blinding

To avoid any risk of contamination between the SDM and control groups, cluster randomization will be implemented in this trial. The intervention provided to patients with AF will be grouped by clinicians in a single community health service center. Computer-generated randomization will be used to allocate the intervention and control groups in a 1:1 ratio following AF confirmation. The allocation results of each community health center will be told to the administrators by telephone. Each administrator only knows the result of his or her own site. The researchers, participants, and data analysts will not be blinded, but the participants will not be allowed to know the outcomes of this study.

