### Statistical analyses

In accordance with standard practice, continuous variables will be presented as means ± standard deviation, while categorical variables will be expressed as proportions. The Kolmogorov–Smirnov test will be utilized to determine the normality of the data. Student’s *t*-test or Mann–Whitney’s *U*-test will be applied to compare two groups, depending on the distribution of the data. For categorical data, comparisons between the groups will be performed using the chi-square or Fisher’s exact tests. Time in therapeutic range (TTR) will be evaluated for patients on warfarin. Multiple imputations will be used to fill in missing values, and both per-protocol (PP) analysis and intention-to-treat (ITT) analysis will be conducted. Subgroup analyses will be performed based on patients’ age groups, treating hospitals, liver or kidney function, the type of anticoagulants used, etc. Statistical significance will be assumed for *p* values less than 0.05. All statistical analyses will be conducted with the IBM SPSS version 22.0 software.

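### Eight openly allocated centres with no stated stratification are compared by unadjusted tests, although prognostic day-0 values are collected

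*Protocol article*

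**What the plan says.** All references are to the protocol article.

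- **Unit.** The abstract gives "440 patients with AF in 8 community health service centers (clusters) in Shanghai, China", so 1:1 means four centres against four. Interventions also describes centres as the randomized unit.
- **Allocation.** Randomization and blinding says that a computer-generated scheme is used "to allocate the intervention and control groups in a 1:1 ratio following AF confirmation". Each centre's result is telephoned to its administrator. Researchers, participants and analysts are all unblinded. No stratification, matching or constraint is mentioned.
- **Recruitment.** A cardiology doctor from each centre, with a clinical pharmacist, oversees recruitment of about 3 patients per centre per month for 18 months. The routes are records, mailings, calls, referral and "advertisements on online platforms and social media, such as WeChat Official accounts, will be used to raise awareness". Study design says "Consecutive patients with AF will be enrolled in the study".
- **Eligibility.** In Settings and participants, patients must "have received a new diagnosis of paroxysmal, persistent, or permanent AF confirmed by electrocardiogram". Table 1 has "Diagnosed with new-onset, paroxysmal, persistent, or permanent AF confirmed with electrocardiogram". The text also excludes patients who could not follow the study's demands; Table 1 has no such line.
- **Day-0 data.** Table 3 schedules age, comedications, liver, kidney and heart function, CHA2DS2-VASc, HAS-BLED, AKT, MARS-5 and ACTS.
- **Analysis.** In Statistical analyses, a t-test or Mann–Whitney test "will be applied to compare two groups, depending on the distribution of the data", and categorical data get chi-square or Fisher's exact tests. Age, hospital and organ function appear only as subgroup factors. No covariate, baseline score or centre term is named for the arm comparison.

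**The concern.** With only four centres per arm, randomization cannot be relied on to balance patient characteristics, because patients within a centre resemble one another and few units are being shuffled. Two features add to this. The people enrolling patients are unblinded and probably know their centre's arm. The entry criterion also exists in two wordings, so there is room for judgement about who qualifies.

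Bleeding risk at entry and the questionnaire scores at entry plausibly predict the outcomes. If they differ between arms, an unadjusted comparison carries the difference straight into the estimated effect. The plan collects the variables that would remove much of the measured part and then leaves them out of the named comparisons.

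**Working it through.** **1. The plan's own sample size.** Inputs from Sample size: 20% control bleeding, a 15% reduction read as percentage points (20% to 5%), two-sided 5%, power 80%, 20% loss, design effect 2.

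- Uncorrected n per arm = [1.96 × √(2 × 0.125 × 0.875) + 0.842 × √(0.16 + 0.0475)]² / 0.15² ≈ 75.1, rounded up to 76.
- With the continuity correction: (75.1/4) × [1 + √(1 + 4/(75.1 × 0.15))]² ≈ 88.
- 88/(1 − 0.20) = 110; 110 × 2 arms × 2 = 440.

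The stated 440 reproduces, so this point does not rest on an arithmetic error.

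**2. Clustering implied by the plan.** Patients per centre = 440/8 = 55. Design effect = 1 + (55 − 1) × ICC = 2, so ICC = 1/54 ≈ 0.0185.

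**3. Chance imbalance at day 0.** With 220 patients per arm, the SD of the between-arm difference in a standardised covariate is √[(2/220) × (1 + 54 × ICC)]. By a normal approximation, the probability of a gap above 0.2 SD in either direction is:

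| ICC of the covariate | Design effect | SD of difference | P(gap > 0.2 SD) |
|---|---|---|---|
| 0 (individual randomization) | 1 | 0.095 | 3.6% |
| 0.01 | 1.54 | 0.118 | 9.1% |
| 0.0185 (plan's design effect) | 2 | 0.135 | 13.8% |
| 0.05 | 3.7 | 0.183 | 27.5% |
| 0.10 | 6.4 | 0.241 | 40.7% |

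For a trait with 50% prevalence (SD 0.5), 0.2 SD is a 10-point gap. The documents give no covariate ICC, so the 0.0185 row assumes that the covariate clusters as the design effect for bleeding implies.

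**4. What a gap could do to the primary result (assumptions).** The documents give no covariate–bleeding association. Suppose bleeding risk is 15% v 25%, or 10% v 30%, without and with a high-risk trait.

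- A 10-point gap gives 0.10 × 0.10 = 1 point or 0.10 × 0.20 = 2 points of spurious difference.
- A 20-point gap at the wider contrast gives 0.20 × 0.20 = 4 points.
- At effective n = 88 per arm, SE = √(2 × 0.2 × 0.8/88) = 0.060. A fixed bias of 1, 2 or 4 points moves a nominal 5% test to about 5.3%, 6.3% or 10.2%.

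**5. Order of allocation and enrolment.** A centre can be allocated only once, while its patients arrive at 440/18/8 = 3.06 per month over 18 months. Even if a centre's first confirmed case triggered its allocation, nearly all later patients would meet staff able to know the arm. This is inferred; the article does not state the order.

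**6. The two entry wordings.** In the text, newness qualifies every AF type. In Table 1, new-onset is one of four alternatives, so established AF is admitted. Both cannot define the same population.

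**The case against.** **Covariates belong in the analysis plan.** Covariate lists and repeated-measures models are usually set there, an unseen plan may contain them, and naming simple tests does not forbid adjusted models. That is fair as to detail. What stands is that the article does name the tests for its group comparisons, and every one is unadjusted.

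**Chance imbalance is not bias.** A test whose standard error respects clustering already allows for it. That is correct in the long run, but the tests named do not respect clustering. Adjustment also removes the measured imbalance present in the one trial actually run. The missing centre term is a related but separate fault.

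**The effect is small.** The illustrative 1 to 2 points are modest against a planned 15-point difference. That stands, and it makes this an improvement rather than a fatal flaw.

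Some stronger readings are tempting but unsupported:

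- A reader might infer that the arms apply different eligibility rules. The two wordings cover all centres, and nothing says that they are applied differently by arm.
- A reader might treat recruitment after allocation as stated. It is inferred.
- A reader might see a contradiction between consecutive enrolment and advertising. Recruitment starts from medical records, the other routes may simply reach eligible patients, and nothing says that advertisements mention the tool.
- A reader might put a figure on differing anticoagulant use at entry. That needs a bleeding risk off anticoagulants, which the documents do not give, and assumes that entry status persists although treatment is re-evaluated at follow-up.

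**Conclusion.** The point holds in this form: eight openly allocated centres, no stated stratification, enrolment by unblinded centre staff very probably after the arm is known, and only unadjusted tests named although prognostic day-0 data are collected.

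The firm number is the chance of imbalance: about 14% for a gap above 0.2 SD at the plan's own design effect, roughly four times the 3.6% under individual randomization. It rests on 55 patients per centre, a normal approximation and a covariate ICC of about 0.0185. The effect on the bleeding comparison can be shown only under assumed risks.

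The eligibility conflict and the unclear timing of allocation are real defects of wording. Whether selection differed between arms cannot be determined from the article. This should be changed before analysis.

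**What to change.** 1. **Primary outcome.** Pre-specify a bleeding model adjusted for a short list of day-0 covariates already collected: age and HAS-BLED. HAS-BLED contains an age item, so the overlap should be acknowledged. Add anticoagulant use at entry only if it is recorded at day 0; Table 3 does not itemise it. Account for centre with a small-sample correction for eight clusters, for example a covariate-adjusted centre-level comparison on 8 − 2 = 6 degrees of freedom.
2. **Questionnaires.** Adjust AKT for its day-0 score. Do the same for MARS-5 and ACTS only in patients for whom a day-0 score is meaningful, and state a rule for patients not yet anticoagulated, who may have no treatment to report on.
3. **Eligibility.** Reconcile the text with Table 1, on the new-diagnosis wording and on the exclusion missing from the table. Report which version each centre applied.
4. **Allocation.** State that centres were allocated once, and when this was relative to patient identification and consent.
5. **Limitation.** Acknowledge that adjustment corrects measured imbalance only; selection on unmeasured factors would remain.

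**Cost.** Age and HAS-BLED need no new data. The adjusted result is slightly harder to present. Enrolment began in October 2022 (Trial status), so for patients already enrolled items 3 and 4 can only be reported, not changed.
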